##### • Oral Glucose Tolerance Test (OGTT)

An OGTT will be performed after a fasting period of at least 10 hours. Blood samples will be collected in the fasting state and 30, 60, 90, 120 and 180 minutes after ingestion of a glucose drink (100 g D-glucose in 0.5 l water). Participants should not eat anything or do any physical activity or exercise during the test. The insulin sensitivity index will be calculated from a 100-g OGTT according to the equation derived by Matsuda and DeFronzo [35] in which insulin sensitivity is estimated by using the fasting and mean glucose and insulin concentrations in serum and HOMA-index. Simple fasting method to measure insulin resistance is the homeostasis model assessment (HOMA) (= fasting insulin concentration (μU/mL) × fasting glucose concentration (mmol/L)/22.5)) [36].

### Process evaluation

To assess factors that contribute to the success or failure of the program, a process evaluation will be performed. Trainers and a subgroup of 20 women will be interviewed about their experiences with the exercise program. Attendance to the exercise sessions will be recorded by the physiotherapists. Furthermore, 10 women who have declined to participate in the RCT will be interviewed about their reasons for declining, and their possible barriers towards participating in an exercise program.

### Statistical analysis

Longitudinal, linear regression analyses will be performed. In these analyses, the correlation between multiple measurements within one individual is taken into account. The regression coefficient reflects the average difference in the outcome variable between conditions. Possible confounders will be entered into the regression analyses. Confounding will be defined as a change in the regression coefficient of 10% or more. Possible effect modification will be studied as well, defined as a significant (p < 0.10) interaction-term between group allocation and the variable concerned. Data will be analysed according to the intention-to-treat principle.

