### Sample size

Power analysis is based on the effects of the intervention program on fasting plasma glucose. A difference of 0.4 mmol/l in fasting plasma glucose between the two research groups is considered to be clinically relevant. Assuming a standard deviation of 0.7 mmol/l, this difference can be detected with a power (1-β) of 0.80 and an alpha of 0.05 with two groups of 64 subjects. Taking a loss to follow up of about 20% into account, a total of 160 subjects will be recruited. A significant difference of 300 grams in birth weight can also be detected with this number of participants, assuming a standard deviation of 600 grams.

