### Intervention

#### Intervention Group

Participants randomised to the intervention group will complete an exercise program on two days of the week during the remaining duration of the pregnancy. Each session will last for 60 minutes. The exercise program will consist of aerobic and strength exercises that will help to control the blood glucose level. All sessions will be completed under the guidance and supervision of a specifically trained physiotherapist. The sessions will be located at the Department Physiotherapy of the participating hospitals (VUMC, OLVG and SLAZ).

At the first session the participants will be introduced to the exercise program. They will be informed about the structure of the sessions and will receive instructions in the use of the equipment. Each exercise session will begin with a warming-up for 5–10 minutes. This is a light intensity activity, such as slow cycling at a level of intensity of 50 Watt, that prepares the muscles for exercise. After the warming-up, each participant completes an individualised program of 40 minutes, consisting of 1 or 2 aerobic exercises and 4 to 6 strength exercises. After exercising, participants cool down for 5–10 minutes by slowly reducing the activity. This allows the heart rate to return to normal levels.

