#### Control group

The control group will receive usual care given by obstetricians and midwives. Dutch midwives and obstetricians follow closely the health status of each pregnant woman and their unborn child. The first appointment is usually between 9^th ^and 12^th ^week of gestation. For women who develop GDM during the study, usual care consists of dietary advice and insulin treatment. Every treatment will be registered in the medical records.

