### Outcome measurements

Participants in both intervention and control group are invited for three measurement appointments during pregnancy and one appointment after pregnancy (see Table 1). Outcome measurements are assessed at baseline (around 15 weeks of pregnancy), 24 and 32 weeks of pregnancy and 12 weeks postpartum by means of physical measurements, laboratory tests, and self-administered questionnaires.

**Table 1 T1:** Schedule of measurements.

**T0: 15 weeks pregnancy**	**T1: 24 weeks pregnancy**	**T2: 32 weeks pregnancy**	**T3: 12 weeks post partum**
Fasting blood sample	OGTT*	OGTT	Fasting blood sample
	Ultrasound*	Ultrasound	Neonatal weight**
Maternal weight	Maternal weight	Maternal weight	Maternal weight
Accelerometer	Accelerometer	Accelerometer	Accelerometer
Questionnaire	Questionnaire	Questionnaire	Questionnaire

*measurement as part of usual care in hospital; **weight of the baby at delivery, as part of usual care.

*Primary maternal outcome *measures are fasting plasma glucose and relative increase in insulin resistance. *Primary neonatal outcome *is birth weight.

*Secondary outcome *measures are: maternal serum triglycerides, HDL, cholesterol and HbA1c, maternal weight gain during pregnancy, maternal physical activity level, foetal growth. Changes in direct health care and non-health care costs and indirect non-health care costs are studies as well.

Although the groups are too small to be able to detect statistically significant changes in these outcomes, the following variables will be assessed as well because of their clinical importance: incidence of gestational diabetes, macrosomia (97^th ^percentile for gestational age), and complications during pregnancy or delivery, such as preeclampsia, caesarean section rate and need for labour induction. These outcomes will be collected from the medical records of the gynaecologist or midwife.

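### The fasting glucose effect is one averaged coefficient, not restricted to on-programme visits, and adjustment for baseline glucose is left to a 10% change rule

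*Protocol article*

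**What the plan says.** The Statistical analysis section plans longitudinal linear regression that allows for within-woman correlation, and defines the effect: "The regression coefficient reflects the average difference in the outcome variable between conditions". Possible confounders are entered, and confounding means a change of at least 10% in that coefficient. Interaction terms appear only in the search for effect modification. The analysis is by intention to treat.

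The schedule is given under Outcome measurements: "Outcome measurements are assessed at baseline (around 15 weeks of pregnancy), 24 and 32 weeks of pregnancy and 12 weeks postpartum". Table 1 there shows fasting samples at T0 and T3 and an OGTT at T1 and T2. The Laboratory tests section confirms that the OGTT includes a fasting sample, so fasting glucose exists at all four visits.

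T0 comes before allocation (Study design). The programme runs "during the remaining duration of the pregnancy" (Intervention Group), so it has ended by T3.

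The Sample size section sets the target: "A difference of 0.4 mmol/l in fasting plasma glucose between the two research groups is considered to be clinically relevant". It names no visit. The article also does not list the visits that enter the model as outcomes, and it does not mention the baseline value of the outcome.

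**The concern.** The four glucose values do not carry the same information about the programme. The expected group difference at T0 is zero because of randomisation. T1 and T2 measure women on the programme, which is what the stated aim is about. T3 measures them after it has stopped. A single average over visits that are not named can therefore mix a visit with no effect, two with the effect of interest and one with an unknown residual effect. The trial is sized for a difference of 0.4 mmol/l, not for 0.4 diluted in this way.

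The second issue is baseline glucose. It is likely to be the strongest predictor of later glucose, but the only route into the model is a rule that looks at how far the estimated effect moves. The examples of confounders in the Questionnaire section (age, ethnicity, socio-economic status, working status, parity) do not include it. At stake are the size, precision and meaning of the result for the primary outcome on which the power analysis rests.

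**Working it through.** **Inputs from the Sample size section.** Target 0.4 mmol/l and SD 0.7 mmol/l, to be detected "with a power (1-β) of 0.80 and an alpha of 0.05 with two groups of 64 subjects"; the recruitment figure of 160 allows for roughly 20% dropout. The test is taken as two-sided.

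**The plan's own figure.** n per group = 2 × (1.96 + 0.84)² × 0.7² / 0.4² ≈ 48.1, so 49 (50 with the t distribution). With 64 per group, SE = 0.7 × √(2/64) = 0.124 and power = Φ(0.4/0.124 − 1.96) ≈ 0.90. The stated 64 does not follow from the glucose inputs. It does match the birth weight inputs (300 g, SD 600 g: 63 to 64 per group). That is a separate matter. Here it only means that the benchmark for one glucose comparison is about 0.90.

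**Assumptions not in the document.** SD 0.7 at every visit; exchangeable within-woman correlation ρ of 0.3, 0.5 or 0.7; true effect 0 at T0, 0.4 at T1 and T2, and 0 at T3 (varied below).

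**Formulas.** Under exchangeable correlation a common group coefficient weights the k outcome visits equally.
- Without T0 as covariate: SE² = (2/64) × 0.49 × (1 + (k − 1)ρ)/k
- With T0 as covariate: SE² = (2/64) × 0.49 × (1 − ρ)(1/k + ρ)
- Power = Φ(estimate/SE − 1.96)

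Worked case, all four visits, ρ = 0.5: estimate = (0 + 0.4 + 0.4 + 0)/4 = 0.20; SE = √(0.03125 × 0.49 × 2.5/4) = 0.098; power = Φ(2.045 − 1.96) = 0.53.

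| Reading | Estimate | SE at ρ = 0.3 / 0.5 / 0.7 | Power |
|---|---|---|---|
| A. T0 to T3 all outcomes | 0.20 | 0.085 / 0.098 / 0.109 | 0.65 / 0.53 / 0.45 |
| B. T1 to T3 outcomes, T0 unused | 0.27 | 0.090 / 0.101 / 0.111 | 0.84 / 0.75 / 0.67 |
| C. T1 to T3 outcomes, T0 covariate | 0.27 | 0.082 / 0.080 / 0.069 | 0.90 / 0.92 / 0.97 |
| D. T1 and T2 outcomes, T0 covariate | 0.40 | 0.093 / 0.088 / 0.074 | 0.99 or more |

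**Sensitivity to the T3 effect.** In A, a T3 effect of 0.2 gives (0.4 + 0.4 + 0.2)/4 = 0.25, with power 0.83 / 0.72 / 0.63. A T3 effect of 0.4 gives 0.30, with power 0.94 / 0.87 / 0.79. In C, the same two effects give 0.33 and 0.40.

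**Sensitivity to the correlation structure.** AR(1) gives more weight to the first and last visits. With a T3 effect of 0, A becomes 0.165 / 0.133 / 0.092, with power 0.58 / 0.33 / 0.15. C becomes 0.26 / 0.27 / 0.30, with power 0.87 / 0.86 / 0.96.

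**Baseline.** The chance difference at T0 has SE 0.124, so a 95% range of ±0.24 mmol/l, about 60% of the target. Adjustment moves a follow-up difference by roughly ρ times the imbalance. At ρ = 0.5 and a coefficient of 0.4, the 10% threshold (0.04) is reached at an imbalance of 0.04/0.5 = 0.08. Below that, T0 stays out and its precision is lost: for the mean of T1 and T2 the SE is 0.107 without T0 and 0.088 with it.

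**The case against.** The strongest reply is that the article never says T0 or T3 is an outcome and never excludes baseline adjustment. It is a condensed text, and the modelled visits may be fixed in the full protocol or analysis plan. This stands. A reader might infer from the schedule, where baseline is listed among the outcome measurements, that all four visits are pooled and the effect is therefore halved. The schedule says when measurements are taken, not how they enter the model. Halving also needs a zero T3 effect and equal weights.

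A large baseline imbalance would probably trigger the 10% rule: 0.24 × 0.5 = 0.12, or 30% of 0.4. This also stands, but it shows that adjustment depends on the data, and the rule gives no precision when the imbalance is small.

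Some effect may persist to T3, since women are also encouraged to be active in daily life, and a time-averaged difference is a legitimate estimand. Both are fair. Reading C also keeps power above the planned 0.80, so a general claim that the trial loses power is not supported. What remains under C is dilution: unless the effect persists in full, the coefficient is not the on-programme difference.

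A reader might also infer that 32 weeks alone should be primary, or that glucose values after the start of GDM treatment should be set aside, because "For women who develop GDM during the study, usual care consists of dietary advice and insulin treatment". The Intervention section provides usual treatment in the exercise group too, and the analysis is by intention to treat. These are trade-offs, not errors in the plan. They are a reason to show 24 and 32 weeks separately beside their mean.

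**Conclusion.** The point holds for fasting plasma glucose, and for other outcomes measured at all four visits, such as physical activity. The article commits to one averaged coefficient, does not tie it to on-programme visits, and leaves adjustment for the baseline value to a data-dependent rule.

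The size depends on a choice that the article does not state. A true on-programme difference of 0.4 mmol/l is estimated as about 0.20 if T0 and T3 are both outcomes, and as about 0.27 if T0 is a covariate and T3 is kept. Both figures assume no effect at T3 and exchangeable correlation. In the first case power is about 0.45 to 0.65; in the second it is about 0.90 or more, so the harm there is mainly to the meaning of the estimate.

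A reader might extend this to every primary outcome. It does not apply to birth weight, which is measured once. The dilution does not apply to the OGTT-based index, which exists only at T1 and T2.

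**What to change.** State in the Statistical analysis section that, for fasting glucose:
- the T0 value is always a covariate, outside the 10% rule;
- T1, T2 and T3 are the outcomes, with visit and group-by-visit terms;
- the primary effect is the group difference averaged over 24 and 32 weeks, with each visit also shown;
- T3 is reported separately as a post-programme secondary result.

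Intention to treat is unchanged. The cost is analysis wording only, because every value is already scheduled. The small downside is that the primary result no longer covers the postpartum visit.

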### Randomisation

A computerized random number generator draws up an allocation schedule pre-stratified for the hospital where participants will be measured or where they will follow the exercise program; within hospitals respondents will be allocated at random to either the intervention or to the control group. Block randomisation in blocks of four will be performed. After baseline measurements, a research assistant will inform the women about the group they will be allocated to.

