#### Questionnaire

• Physical activity will be assessed with the Activity Questionnaire for Adolescents & Adults (AQUA) [31].

• Quality of life will be assessed with the EuroQol [32,33].

• All costs related to pregnancy and delivery: direct health care and non-health care costs and indirect non-health care costs. Examples of direct health care costs are costs for visits to the general practitioner, medical specialists, therapists, dieticians, costs of medication and hospitalisation. Examples of direct non-health care costs are the costs of over-the-counter medication, travel time, and waiting time. Indirect costs will include the costs of absence from paid and unpaid work. Costs will be calculated by multiplying the volume of resource use by cost prices, following the Dutch guidelines for economic evaluations in health care to estimate costs [34].

• Potential confounding variables such as age, ethnicity, socio-economic status, working status, and parity will be measured also.

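### The model for a randomised comparison is chosen by a 10% change in the treatment coefficient, so it is not fixed in advance and depends on chance imbalance and on the effect itself

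*Protocol article*

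**What the plan says.** The Statistical analysis section of the protocol article plans longitudinal linear regression and explains its coefficient: "The regression coefficient reflects the average difference in the outcome variable between conditions". It then says "Possible confounders will be entered into the regression analyses" and gives the criterion: "Confounding will be defined as a change in the regression coefficient of 10% or more".

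The candidates appear in the Questionnaire section as an open list: "Potential confounding variables such as age, ethnicity, socio-economic status, working status, and parity will be measured also".

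The Randomisation section says the schedule is "pre-stratified for the hospital where participants will be measured or where they will follow the exercise program", that "within hospitals respondents will be allocated at random to either the intervention or to the control group", and that "Block randomisation in blocks of four will be performed". The Outcome measurements section and its Table 1 place a fasting blood sample at about 15 weeks (T0), so fasting glucose has a baseline value.

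**The concern.** A change-in-estimate rule is meant for observational data, where a covariate can be systematically related to exposure. Here exposure is allocated at random within hospital, so a baseline difference between the arms arises by chance. A 10% shift then measures chance imbalance multiplied by prognostic strength.

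Two consequences follow. First, the threshold is 10% of the treatment estimate itself, so the same imbalance passes when the effect is small and fails when it is large. The covariate set thus depends on the quantity being estimated. Second, a strongly prognostic but well-balanced covariate is left out, although it would reduce residual variance. What is at stake is a model settled only after its effect on the treatment difference has been seen, and a standard error computed as if that model had been given beforehand.

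**Working it through.** **Inputs from the protocol (Sample size).** Difference 0.4 mmol/l, SD 0.7 mmol/l, 64 per group, alpha 0.05 (taken as two-sided). The planned effect is 0.4/0.7 = 0.571 SD.

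**Assumed, not in the protocol.** The correlation r between a covariate and the outcome. Values from 0.1 to 0.7 were tried; 0.6 and 0.3 are the main cases.

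**The plan's own figure.** 2 × (1.96 + 0.842)² / 0.571² gives 49 per group (50 by t-test), not 64. With 64 per group, unadjusted power at 0.571 SD is about 0.90. The figure of 64 is the t-test size for 300/600 = 0.5 SD, the birth weight case. This is a separate matter and serves here only as the unadjusted reference. The step 64/0.80 = 80 per group, 160 in total, does reproduce.

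**Closed-form check of the rule.** Work in outcome SD units with a standardised covariate. The chance imbalance D between the arms has standard deviation √(2/64) = 0.177. Adding the covariate moves the treatment coefficient by about r × D.

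- *Planned effect.* The threshold is about 0.1 × 0.571 = 0.057. The covariate enters with probability P(|Z| > 0.057/(0.177 r)). For r = 0.6 this is P(|Z| > 0.54) = 0.59; for r = 0.3 it is P(|Z| > 1.08) = 0.28.
- *No effect.* The estimate is itself noise. Taking the 10% relative to the adjusted estimate, the probability is (2/π) × arctan(10r/√(1 − r²)). For r = 0.6 this is (2/π) × arctan(7.5) = 0.92; for r = 0.3 it is (2/π) × arctan(3.14) = 0.80.

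**Simulation.** 64 per arm, one follow-up value, a baseline covariate with correlation r plus five weak covariates (0.1 to 0.2), and all covariates that pass entered together.

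| True effect (SD) | r | Baseline enters, closed form | Baseline enters, simulated |
|---|---|---|---|
| 0.571 | 0.6 | 0.59 | about 0.57 to 0.59 |
| 0.571 | 0.3 | 0.28 | about 0.30 |
| 0 | 0.6 | 0.92 | about 0.90 to 0.91 |
| 0 | 0.3 | 0.80 | about 0.78 |

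At r = 0.6 the rule keeps on average 1.1 of 6 covariates at the planned effect, 2.4 at half of it and 3.7 at none.

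**Calibration at the planned effect.** At r = 0.6 the mean reported standard error is 0.155 SD against an actual spread of 0.140, a ratio of 1.11. Repeats gave 0.154 against 0.140 to 0.142, that is 8% to 10%. The 95% interval covers about 96.5%. At r = 0.3 the excess is about 1%.

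**Error rates.** Rejection under no effect is 0.040 to 0.043 in the six-covariate case at r = 0.6, and 3.9% to 5.4% over all scenarios tried. Bias is at most about 0.005 mmol/l, or 0.005/0.7 = 0.007 SD, in most settings and about 0.01 SD or less throughout.

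**Power at the planned effect, rule against baseline fixed.** 0.98 and 0.98 at r = 0.6; 0.92 and 0.92 at r = 0.3. With a single candidate covariate it is 0.91 and 0.92 (r = 0.3), 0.95 and 0.96 (r = 0.5), 0.99 and 0.99 (r = 0.7). At half the planned effect (0.2 mmol/l) a single strong covariate shows a gap: 0.42 against 0.45 at r = 0.5, and 0.55 against 0.61 at r = 0.7.

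**The case against.** The best defence is that the rule does little measurable harm. At the planned effect it gives about the power of a model with baseline fixed, because baseline is left out mainly when it is balanced, and then omitting it hardly moves the estimate. The standard error errs on the conservative side. This stands, and it limits the severity.

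A threshold stated in advance also restricts the analyst more than free choice would, and the Blinding section plans analyses blind to allocation. That too stands against any suggestion of steering towards one arm. It does not make the model independent of the data, and the open candidate list leaves the outcome of the rule undetermined.

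A reader might infer that the protocol leaves out baseline and hospital. That cannot be concluded. The list is illustrative and sits among questionnaire items, and a condensed article may leave the covariate list to a fuller plan. The absence of these terms only supports the point. The selection rule itself is different: it is stated, so a fuller plan could only reverse it.

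Finally, the simulation uses one follow-up value, whereas the protocol plans a longitudinal model and does not say whether T0 enters as an outcome or as a covariate. The sizes are therefore indicative.

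**Conclusion.** The point holds as a fault in a stated method. In a randomised comparison the rule reacts to chance imbalance and to the size of the estimate, so the model is data-dependent and its standard error does not describe the selection step. At the planned effect the intervals can be conservative, by about 10% in standard error if baseline correlates 0.6 with the outcome and by about 1% at 0.3. Both correlations are assumptions.

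Two stronger readings are not supported. One is that the rule produces false positives or material bias: neither appeared in any scenario tried. The other is that it costs substantial power, for instance a standard error of 0.176 against 0.142 SD (24% wider) and power of 0.90 against 0.98. Those figures compare never adjusting for baseline with always doing so; they do not describe this rule. Any power cost of the rule itself is negligible at the planned effect and reaches a few percentage points at half of it when the covariate is strong.

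The baseline argument applies clearly to fasting glucose only. Birth weight has no baseline value, and the relative increase in insulin resistance already refers to an earlier value. The change is worth making because it costs almost nothing, not because the trial's conclusion is in danger.

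**What to change.** Remove the 10% criterion from the primary analyses and name the covariates in advance: the T0 value of the outcome where it exists and is not already part of the outcome (fasting glucose), and the hospital used for stratification. Any further prognostic covariates should form a short list named before the data are seen. The change-in-estimate analysis may be kept as a sensitivity analysis.

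The cost is one sentence in the Statistical analysis section and a few degrees of freedom among about 128 women (2 × 64).
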